### Ethics Approval

The study was approved by the institutional review board at Emory University (STUDY00004750) and registered at the CliniclTrials.gov (NCT05663203). Participants will be recruited from May 2023 to August 2024 at the Emory Winship Cancer Institute. The research staff will screen eligible patients in the electronic health record system (Epic); they will then reach out to health care providers at the clinic who will confirm eligibility and suitability and give permission for the research staff to reach out to the patient-caregiver dyads to assess their interests. If the research staff find that both patients and caregivers are interested, they will explain the study to dyads and obtain dyads’ written informed consent in person at the clinic.

### Phase 1—CRCweb Development

#### Semistructured Interviews

We will conduct semistructured interviews with patient-caregiver dyads using an interview guide developed from the existing literature that includes open-ended questions and probes. Dyads (n=8) will be asked about their needs for the intervention, perspectives, and suggestions for a web-based intervention to manage their symptoms, what they like and do not like about the proposed CRCweb intervention components (ie, family involvement, symptom management, and coping effectiveness) and delivery mode (eg, doses and intervals), and what modifications they would recommend being made. The interview will last 30 to 45 minutes and be conducted by the principal investigator (PI) in a private conference room at the clinic or in a Zoom meeting based on the dyad’s preference. All interviews will be audio recorded and transcribed, and field notes will be taken to capture nonverbal expressions.

#### Development of a CRCweb Prototype

We will develop the CRCweb prototype and deploy it to Amazon Web Services (AWS) at Emory. AWS at Emory is a certified cloud service provided by AWS. A technology expert (WC) who has developed several rigorous web programs such as TCOLA (a technology-based CRC support program for Asian American women) will provide technical support. Two full-stack web designers will develop the CRCweb prototype (in 4-6 months). We will also collaborate with Health Information Technology Core at Emory University School of Nursing for the web program development. The research team will review the CRCweb prototype to provide feedback and make modifications.

#### Usability Testing

After the CRCweb prototype is developed, we will ask 4 patient-caregiver dyads to use the CRCweb prototype and provide feedback about the usability of the program [34]. Semistructured interviews (30-45 minutes) will probe for participants’ experiences with using CRCweb (eg, design, navigation, structure, and language). Interviews will be recorded and transcribed; field notes will capture dyads’ interactions with the program and document problems with using the websites. Five clinicians or researchers in oncology area will serve as content experts and provide feedback on the program. Feedback will guide the refinement of the CRCweb program, yielding a final version that will be used in the clinical trial.

### Phase 2—Pilot Clinical Trial

We will conduct a single-arm, nonrandomized, and nonblinded pre- and posttest clinical trial among patients with CRC receiving chemotherapy and their caregivers (n=20 dyads). Primary outcomes (feasibility and acceptability) will be assessed at the completion of intervention among patients and caregivers. Secondary outcomes (PNS and QOL) will be assessed at baseline (T1, before intervention) and 8 weeks (T2, after intervention) for patients and caregivers. We will collect quantitative assessment data on internet-accessible devices via REDCap self-administered surveys. We will avoid collecting symptom data at the acute symptoms stage (within 1 week after chemotherapy administration) to reduce measurement bias. Additionally, semistructured formative evaluation interviews will be conducted after the intervention among these participants regarding their experiences and suggestions on the intervention to inform the future refinement.

#### Intervention

CRCweb is designed to create opportunities for patients and caregivers to obtain information and interact with each other. Patient-caregiver dyads (n=20) will participate together in an 8-week CRCweb intervention using assigned accounts and passwords to access to CRCweb with the help of the research staff. An introductory video (5 minutes) on the CRCweb page will teach patients and caregivers how to use CRCweb and navigate the websites. Dyads can use the program at any time and any place during the 8 weeks. They are encouraged to log on the program using their own devices and complete modules together, sitting side by side if possible. Three modules (ie, family involvement, symptom management, and coping strategies) are selected because they are more relevant to symptom management. Each module will be presented 2 weeks apart to enable dyads to absorb the information sequentially and practice the module’s principles before moving to the next module. The content of modules is shown in Table 2. Each module has 4 sections: video-enhanced lectures (10-20 minutes) and audio-enhanced texts, resources and web links, assignments, and evaluations. The video-enhanced lectures and audio-enhanced texts contain the same contents, allowing users to acquire the material according to their own learning styles. Modules include relevant resources and web links (eg, organizations, guidelines, and support services) for those who want additional information and resources. The modules for patients and caregivers are the same except tailored resources and web links. Assignments encourage dyads to practice learning skills and activities, discuss the symptoms and their effects on their daily lives, and brainstorm strategies to minimize the negative effects. After each module, a self-evaluation survey (score range 0-10) assesses the dyad’s learning. If they receive a score 0 to 5, a reminder message appears suggesting they take more time in the next week to review the module; if the score is 6 to 8, they can use the same amount of time next week to review the module; and if the score is 9 to 10, they are ready to move to the next module. We will track website activity data (eg, number of logins and time spent on the site) to assess if patients and caregivers engage in the learning modules. Additionally, we will send them weekly emails or SMS text messages to remind them to complete modules and surveys. The intervention flow is shown in Figure 2.

**Table 2 table2:** Module content.

Module and goal			Content
**Family involvement**			
	Promoting open communication	•Discuss benefits of open communication versus concealment •Emphasize the importance of communication •Encourage open discussion of concerns •Use “I” statements to express feelings, use humor •Encourage sharing perspectives on any issues, concerns, or feelings •Address issues or concerns and reassure feelings	
	Encouraging mutual support and teamwork	•Discuss that cancer can affect both patient and family, making mutual support essential •Recognize the contributions of both members of the dyads and encourage the expression of appreciation	
	Identifying family strengths	•Help patients and family members identify individual and family strengths •Keep up positive outlook and face challenges together	
	Introducing family to information and resources	•Identify resources for the family to manage the recurrent illness •Give names and contact numbers of support groups for patients with colorectal cancer and their family	
**Symptom management**			
	Assessing symptoms	•Assess symptoms experienced by patients and their caregivers •Talk about the most severe, frequent, or distressed symptoms •Discuss effects of treatment on family relationships and the importance of caregiver’s health	
	Teaching self-care strategies	•Review patients’ and their caregivers’ symptom management and learn symptom management strategies •Provide information, guidelines, resources, and support services	
	Establishing realistic and short-term goals	•Set up easy goals to achieve for symptom management •Document and monitor symptoms, write symptom diary	
**Coping effectiveness**			
	Dealing with overwhelming stress	•Encourage day-to-day efforts to cope •Allow opportunities to discuss death and dying issues or concerns	
	Encouraging healthy coping and lifestyle behaviors	•Discuss benefits of active versus passive coping strategies •Educate about the importance of healthy lifestyle behaviors for patients and family members: eating and exercise, sleep and rest patterns, use of chemical substances, and support networks	
	Helping caregivers manage the demands of illness	•Encourage caregivers to accept offers of help from others •Help caregivers identify activities to restore their mental and physical energy (eg, hobbies and recreational activities)	

**Figure 2 figure2:**
[figure not shown]
Flow of the intervention and assessments. AFI: Attentional Function Index; BPI: Brief Pain Inventory; MFI-20: 20-item Multidimensional Fatigue Inventory; PHQ-8: 8-item Patient Health Questionnaire; PSQI: Pittsburgh Sleep Quality Index; SF-12: Short Form-12; SSAI: Spielberger State Anxiety Inventories.

#### Intervention Fidelity

The PI will check CRCweb login information every Friday and send the reminder nudge messages with a checklist to patient-caregiver dyads who have not completed the modules and surveys. Given competing demands on patients and caregivers, we allow them to use CRCweb in their available time and limit the time of learning modules (less than 1 hour per week).

#### Measurement

A demographic questionnaire will be used to collect information such as age, gender, race or ethnicity, marital status, education, employment status, exercise, income, insurance, and dyadic relationships. Medical records will be reviewed for patients’ disease and treatment information, such as cancer sites, cancer stage (TNM, tumor-nodes-metastasis), treatment types, chemotherapy regimens and cycles, surgery, and radiotherapy. The measures that include primary outcomes (ie, attrition, adherence, and satisfaction) and secondary outcomes (ie, PNS and QOL) are shown in Table 1. As indicated, all the instruments are valid and reliable.

### Data Analysis

In phase 1, content analysis will be used to analyze the qualitative data [35,36]. Coding will be conducted by 2 researchers (including the PI) with backgrounds in cancer and qualitative methodology. The NVivo software (QSR International Pty Ltd) will be used to support data analysis, which is completed in four steps:

Data preparation [37]: 2 researchers read the transcripts together to get a sense of the whole picture; they identify key topics and storylines and categorize informational content (eg, patients’ perspectives).Writing memos: using the transcripts and filed notes, 2 researchers write analytic memos and a brief case description of each participant.Coding [38]: 2 cycles of coding will be used. The PI uses a priori codes from the literature and clinical practice to create a codebook. The first cycle includes codes developed a priori coding, descriptively, and in vivo [38]. The second researcher reviews the coding scheme and provides feedback; the PI revises the codebook by adding or combing codes. Once the first cycle of coding is completed, 2 researchers review the findings and develop larger categories of data using pattern coding and theoretical coding [38]. The second cycle will be used to organize and group codes that are similar or shared common characteristics.Categorizing and connecting: 2 researchers construct tables and matrices to organize, condense, and display the codes and data samples into categories; all researchers help search for patterns, trends, and paradoxes across all participants and then summarize the descriptions and develop the themes [39].

In phase 2, quantitative data will be analyzed using SPSS Statistics (version 27.0; IBM Corp). Descriptive analyses will be conducted to determine the frequencies, percentages, means, and SDs of major variables. Feasibility of study attrition and adherence will be assessed by calculating attrition rates, identifying reasons for refusal, and assessing completeness of the data. Accessibility of participant satisfaction will be evaluated by calculating descriptive statistics to summarize responses to the poststudy evaluation items. Pre-post paired *t* tests (and nonparametric equivalents as needed) will be used to evaluate the changes between secondary outcomes (PNS, using the same calculating methods as described in our previous publication [13]) from pre- to postintervention stages for patients and caregivers. We will use dyadic analyses because of the increasing evidence that patients’ and their family caregivers’ responses to illness are interrelated [14]. Time and level (ie, patient vs caregiver) will be treated as within-subject variables to control for the interdependent nature of the data. The main effect by time will be examined to determine the overall effect of intervention on PNS for patient-caregiver dyads as a unit (average scores across dyads) [40]. We will also analyze time-by-level interactions to determine if there will be a differential effect of the intervention on patients’ and caregivers’ outcomes [14]. As needed (for an adjusted analysis), potential covariates (eg, age, insurance, and income) will be included in the planned models as appropriate. Additionally, qualitative data from postintervention interview will use the same analysis as in phase 1. Convergent parallel analysis will be used to compare and merge the quantitative and qualitative data when they have been completed [41]. We will discuss areas of convergence or divergence between the quantitative and qualitative results to refine the intervention.

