## Introduction

Colorectal cancer (CRC) is the third most common cancer and the second leading cause of cancer-related deaths in the United States [1]. Patients with CRC receiving chemotherapy often experience severe and distressing psychoneurological symptoms (PNS) that include fatigue, depression, anxiety, sleep disturbance, pain, and cognitive dysfunction [2-5]. When these multiple co-occurring symptoms are undertreated, they negatively affect functional status, survival rates, and quality of life (QOL) of patients and decrease health outcomes (eg, QOL and mood) of their family caregivers (hereafter “caregivers,” defined as family members or significant others identified by the patients as their primary source of emotional and physical support) [6-8]. Current interventional studies in context of CRC are mainly focused on CRC screening and treatment regimens [9,10]. Limited information is available on symptom management for patients with CRC and their caregivers, which underscores the critical need to develop an innovative and effective intervention to manage PNS for patient and caregiver dyads.

Evidence has shown that PNS may share similar mechanisms, such as increases in proinflammatory responses or neurotransmitter alterations, which partially explains why they cluster together [11,12]. Our prior work shows that depression and fatigue are core symptoms within PNS networks and that PNS are highly interconnected with each other over time, suggesting that symptom management for these clustered symptoms may decrease multisymptom burden at the same time [13]. Moreover, addressing multiple symptoms simultaneously is cost-effective as shown in prior research [14,15]. Although interventions have been developed for managing single symptoms (eg, pain and fatigue) [16,17], little is known about multiple PNS management.

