### Participants and Settings

In phase 1, we will recruit 8 patient-caregiver dyads; in phase 2, we will recruit 20 dyads. The inclusion criteria for patients will be age ≥18 years, diagnosed with CRC (any cancer stage), life expectancy >12 months, receiving active chemotherapy, self-reported at least 2 PNS (based on the symptom measures’ cutoff scores described in Table 1), identified primary caregiver, access to the internet, and fluent in English. Patients who have a Karnofsky Performance Scale score of <50 will be excluded. The inclusion criteria for caregivers will be age ≥18 years, primary caregiver, self-reported at least 2 PNS (based on the symptom measures’ cutoff scores described in Table 1), access to the internet, and fluent in English. Caregivers who have severe diseases such as cancer and heart disease will be excluded. Patients will be recruited at the Gastrointestinal Oncology Clinics of Emory Winship Cancer Institute.

**Table 1 table1:** Measurements.

Outcome and variable				Time point^a^		Description

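### The time-by-level interaction cannot show a differential effect of CRCweb, because in a single-arm design it also contains any difference in background change, and only patients are on chemotherapy

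*Protocol article*

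**What the plan says.** The design is stated under Phase 2—Pilot Clinical Trial: one arm of 20 dyads, with no randomization and no blinding. Symptoms (PNS) and quality of life are secondary outcomes and "will be assessed at baseline (T1, before intervention) and 8 weeks (T2, after intervention) for patients and caregivers".

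The model is described under Data Analysis: "Time and level (ie, patient vs caregiver) will be treated as within-subject variables to control for the interdependent nature of the data". The time main effect is presented there as the overall effect of the intervention on the dyad as a unit. The next step is: "We will also analyze time-by-level interactions to determine if there will be a differential effect of the intervention on patients’ and caregivers’ outcomes". Covariates may be added as needed, with age, insurance and income given as examples.

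Under Participants and Settings, patients must be "receiving active chemotherapy, self-reported at least 2 PNS". For caregivers: "Caregivers who have severe diseases such as cancer and heart disease will be excluded". The Introduction opens its rationale with "Patients with CRC receiving chemotherapy often experience severe and distressing psychoneurological symptoms (PNS" and so on, tying these symptoms to chemotherapy.

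**The concern.** The interaction makes caregivers the comparator for patients. Under Intervention, the two roles receive the same modules apart from tailored resources and links, so a difference in change invites the reading that one role responds better. But the roles also differ over the 8 weeks in an exposure that the article connects with the outcome: patients enter on chemotherapy and caregivers do not receive it. With no control dyads, nothing shows how far patients and caregivers would have diverged without CRCweb.

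Two errors are possible. An identical effect in both roles could be reported as a differential one, or a real difference could be hidden because background change offsets it. The quantitative results are to be merged with the interviews to refine the programme, so a misread contrast could colour that discussion.

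**Working it through.** **Plan's own figure.** There is none to reproduce. The article gives no alpha, effect size, SD or power for this test.

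**What the contrast estimates.** With two times and two levels, the interaction is tested by the mean over dyads of D = (patient change − caregiver change), which is a paired t test. Let τ be the mean intervention effect and β the mean background change over 8 weeks, with P for patients and C for caregivers:

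E(D) = (τP − τC) + (βP − βC)

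The stated inference concerns the first bracket only. Estimating the second would need dyads without CRCweb, and there are none. The same algebra applies to the time main effect, whose expectation is (τP + τC)/2 + (βP + βC)/2.

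**Whether anything in the article removes the second bracket.**
- *Timing rule (Phase 2—Pilot Clinical Trial):* "We will avoid collecting symptom data at the acute symptoms stage (within 1 week after chemotherapy administration) to reduce measurement bias". This limits acute effects. It does not deal with accumulation, a change of regimen, or completion of chemotherapy between T1 and T2.
- *Covariates (Data Analysis):* the named examples do not concern chemotherapy. Naming it would not help, because exposure exists only in patients and coincides with role.
- *Regimens and cycles (Measurement):* these are abstracted from patients' records, but they cannot supply what is missing, for the same reason.

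**Size, as illustration.**

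Inputs from the article: 20 dyads. Assumed: two-sided alpha 0.05; SD of the change score 1 in each role; correlation of changes within dyads ρ from 0 to 0.5; τP = τC; net difference in drift δ = βP − βC in units of that SD.

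SE(D) = √(2(1 − ρ)) / √20
- ρ = 0: √2 / √20 = 0.316
- ρ = 0.5: √1 / √20 = 0.224

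The rejection probability comes from the noncentral t with 19 df, critical value 2.093 and noncentrality δ / SE:

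| δ (SD) | noncentrality, ρ = 0 | noncentrality, ρ = 0.5 | chance of a significant interaction |
|---|---|---|---|
| 0 | 0 | 0 | 5% |
| 0.15 | 0.47 | 0.67 | 7-10% |
| 0.3 | 0.95 | 1.34 | 15-25% |
| 0.5 | 1.58 | 2.24 | 32-56% |

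With 17 dyads, the fewest that exceed 80% retention of 20, the three non-zero rows become 7-9%, 13-21% and 28-49%.

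**Simulation check.** With 20,000 runs, 20 dyads, outcome SD 1, T1-T2 correlation 0.6, correlation of changes 0.3 and no intervention effect in either role, a drift of 0.5 gave 51.6% rejections against 51.8% from the formula. The mean estimated interaction was 0.499. The bias is therefore the whole net drift, and recruiting more dyads does not reduce it.

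**The case against.** **This is a declared limit of a pilot.** The article says openly that the trial has a single arm, calls its effects preliminary, makes PNS and quality of life secondary to feasibility and acceptability, and names larger controlled studies as a later step. No feasibility or acceptability criterion uses the interaction. This stands, and it limits the weight of the point. It does not make the stated inference valid, because the Data Analysis section says explicitly what the interaction is meant to determine.

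**Caregivers may drift too.** A reader might infer that patients worsen by a known amount while caregivers stay flat, so that false interactions would be common. The documents do not support that. The Introduction says that undertreated patient symptoms reduce caregivers' health outcomes, Data Analysis calls the members' responses interrelated, and the Discussion says that caregivers' symptoms increase while they care. Only the net difference matters. If caregivers drifted half as much as patients (an assumption), patient drifts of 0.3, 0.5 and 0.7 SD would leave net differences of 0.15, 0.25 and 0.35 SD, and rejection rates of about 7-10%, 12-19% and 18-32%. Patients are also already on chemotherapy at T1. The Introduction supports a high symptom level on treatment, not a worsening from T1 to T2.

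**Module changes would not rest on this test.** A reader might infer that the programme would be revised on a spurious interaction. Refinement also draws on post-intervention interviews and on comparing the two kinds of data, so the risk is one of influence and not of a decision rule.

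**The main effect has the same flaw.** Correct. It calls for correcting both sentences, not for leaving both.

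**Conclusion.** The stated inference is wrong as written. In this design the time-by-level interaction is a difference in pre-post change between roles. It cannot be read as a difference in intervention effect, because chemotherapy differs by role and no comparison group separates the two. This conclusion rests on the design alone and on no assumed figure.

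The sign and size of the bias are unknown. Worsening under chemotherapy would make patients appear to benefit less. Chemotherapy that ended before T2 could make them appear to benefit more. The rates of 7-10%, 15-25% and 32-56% are illustrative: they assume net drifts that the documents do not supply, a change SD of 1, ρ between 0 and 0.5, and equal effects in both roles.

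The consequence is moderate: a secondary analysis in a 20-dyad pilot, with a correction that costs almost nothing.

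**What to change.** In the Data Analysis section:
- Describe the interaction as a *difference in pre-post change between patients and caregivers*, and the time main effect as *mean pre-post change*. Call neither an intervention effect.
- Report mean change for each role with a 95% CI.
- Name background chemotherapy in patients as an alternative explanation for any difference between roles.
- State that the interaction alone will not be used to conclude that CRCweb works better for one role. The planned interviews can inform how well it suits each.
- If patients' change is shown by chemotherapy cycles received, label it descriptive and do not use it as an adjustment. Cycles received after T1 are a post-baseline variable that may itself depend on toxicity or delays, and there are at most 20 patients.

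The cost is a few sentences and confidence intervals from data already collected, with no new assessments or participants. The downside is a weaker claim about who benefits. The causal question is left to a controlled trial.
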